### Measures

Both the primary and secondary outcome measures will be assessed at baseline, 3 and 6 month. The primary outcome measure will be ATS use, assessed using the World Health Organization Alcohol, Smoking, Substance Involvement Screening Test (ASSIST) [28,29]. The ASSIST first assesses lifetime use of nine categories of drugs (i.e. tobacco, alcohol, cannabis, cocaine, ATS, inhalants, sedatives, hallucinogens, opioids and other). Then, for any drug identified by the lifetime question, data relating to the last 3 months is collected on: frequency of use, cravings, problems (health, social legal or financial), and failure to fulfill roles. Next, the ASSIST ascertains if a friend or relative has ever expressed concern about their drug use and if the person has ever tried and failed to control their drug use. Finally, injection of drugs is assessed. The standard ASSIST scoring algorithm will be used to generate a score related to use of ATS [28].

The secondary outcomes will be: (a) health-seeking intention and help-seeking behavior measured with the general help-seeking questionnaire (GHSQ) [30] and the actual help-seeking questionnaire (AHSQ) [31,32]; (b) readiness to change assessed using a modified version of the Readiness to Change Questionnaire (RTCQ) [33] referencing ATS rather than alcohol; (c) psychological distress assessed using the Kessler 10 [34]; (d) poly-drug use measured by the ASSIST [28]; (e) days out of role [35]; and (f) quality of life assessed by the European Health Interview Survey (EUROHIS) Quality of Life scale [36]. The baseline measures include demographic information (e.g., age, sex, marital status), drug use history (age of first use of ATS), and severity of dependence assessed using the Severity of Dependence Scale [37].

Both the GHSQ and AHSQ are designed to be modified to reflect the condition under investigation and relevant potential sources of help [32]. The condition investigated will be help-seeking for ‘a problem with stimulant drug use’, with additions to the existing list of potential sources of help including “drug information services (e.g. internet, telephone)” and “specialist drug services (e.g. in-person services)”. We will also modify examples such as “school counselor” or “teacher” to reflect the target age group (“counselor” or “lecturer”). Item scores will be summed on the two measures. The RTCQ has 12 items, with four questions relating to each of the stages: ‘pre-contemplation’; ‘contemplation’; and ‘action’. The five point Likert scales will be summed to obtain scores on each stage, with participants designated to their highest scoring stage, or in the event to tied scores, the higher stage [33]. The K10 total score (maximum 50) will be used to quantify psychological distress at each time point [34]. Poly-drug use will be defined as the sum of ASSIST classes of drugs endorsed for the past 3 months [29]. ‘Days out of role’ will be derived from Kessler’s questions but referencing “ATS drug use (e.g. methamphetamine, ecstasy, ice) “rather than “depression” [35] and quality of life will be indexed as total EUROHIS Quality of Life scores [36].

In addition, immediately after finishing the third module, the intervention group will evaluate the intervention content and study website. Satisfaction with the intervention plus perceived benefits and negative aspects will be assessed with a measure developed for the *Wellbeing* study [38] but modified to reference “drug use” rather than “depression”. Descriptive measures of completion (e.g. number of modules and subsequently, follow-up surveys) will be collected together with scores on the Internet Intervention Adherence Questionnaire – 16 items evaluating barriers to internet treatment [39]. Table 1 provides a summary of the measures assessed at each time point.

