## Method

### Design

A two-group randomized controlled trial will be used. The intervention group will receive an internet intervention consisting of three modules (detailed below). The wait-list control group will undertake the same assessments as the intervention group, with access to the intervention site at 6 months post enrolment. In addition, all participants will be provided with contact details for emergency services.

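### The summed help-seeking scores include an internet information source with no visible exclusion of the trial's own programme, so an arm difference in this secondary outcome can partly reflect use of the assigned modules

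*Protocol article*

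**What the plan says.** All of this is in the Method section of the protocol article.

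- **Outcome.** Secondary outcome (a) in Measures is "health-seeking intention and help-seeking behavior measured with the general help-seeking questionnaire (GHSQ") together with the AHSQ. On timing: "Both the primary and secondary outcome measures will be assessed at baseline, 3 and 6 month".
- **Items.** Both questionnaires are adapted so that the help in question concerns a stimulant drug problem. Two sources are added to the list. One is "drug information services (e.g. internet, telephone"), the other specialist in-person drug services.
- **Scoring.** "Item scores will be summed on the two measures", so the added source counts in each total.
- **Arms.** Under Design, "The intervention group will receive an internet intervention consisting of three modules"; the wait-list arm gets the intervention site at 6 months after enrolment. Under Procedure, the intervention arm can open the first module at once and is emailed every seven days to start the next module or return to the site. Follow-up is at days 91 and 183 after randomization.
- **Test.** Under Analysis, the intervention effect is read from the time by group interaction.

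**The concern.** The added source describes something the trial gives to one arm. A participant who worked through the modules and is later asked where they turned for help with stimulant use can truthfully point to an internet service. A wait-list participant has no modules to point to until after the last assessment. The summed score can therefore rise in the intervention arm although nobody sought any more help elsewhere.

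The Discussion motivates the trial partly by users' reluctance to approach existing drug services, so a reported rise in help-seeking would attract attention. If part of it is module use, it repeats what the completion measures already record. Neither the mixed model nor the multiple imputation sensitivity analysis can remove this, because it lies in the item and not in the missing data.

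**Working it through.** The article states no figure for the help-seeking outcomes, so there is nothing to reproduce. The check has two parts.

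**1. Does the mechanism follow from the text?**

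| Step | Where stated |
|---|---|
| Help concerns a stimulant problem; the internet is named as a source | Measures |
| Items are summed | Measures |
| Intervention is three internet modules on stimulant use | Design; Content of modules |
| Modules and weekly prompts go to one arm before days 91 and 183 | Design; Procedure |
| Effect is the time by group interaction | Analysis |
| Instruction to leave out the trial's programme | None shown |

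It does. At baseline neither arm has seen the modules. At both follow-ups one arm has. An artefact of this kind falls into the time by group contrast.

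**2. How large could it be?** Only the 60 per group comes from the article (the sample size section). The other inputs are assumptions:

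- the item is scored 0/1;
- a share p0 of both arms truly uses outside internet or telephone services, p0 = 0.10 to 0.50;
- a share q of the remaining intervention participants endorses the item because of the modules, q = 0.10 to 0.50;
- the summed score has SD 1 to 2;
- there is no true difference in outside help-seeking.

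Endorsement in the intervention arm is p1 = p0 + (1 − p0) × q, so the shift in the sum is (1 − p0) × q.

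- Smallest: (1 − 0.50) × 0.10 = 0.05 points.
- Middle: (1 − 0.20) × 0.25 = 0.20 points.
- Largest: (1 − 0.10) × 0.50 = 0.45 points.

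For one two-group comparison at two-sided 5%, z = shift / (SD × √(2/60)), and the rejection rate is Φ(z − 1.96) + Φ(−z − 1.96). For the largest shift with SD 1, z = 0.45 / 0.1826 = 2.465 and the rate is Φ(0.505) ≈ 0.69. All combinations:

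| Shift in sum | SD 1 | SD 1.5 | SD 2 |
|---|---|---|---|
| 0.05 | 0.06 | 0.05 | 0.05 |
| 0.20 | 0.19 | 0.11 | 0.08 |
| 0.45 | 0.69 | 0.38 | 0.23 |

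On the added item alone there is no dilution by the other sources. With p0 = 0.20 and q = 0.25, endorsement is 0.40 against 0.20, and a two-proportion test with 60 per arm rejects with probability about 0.67. Over the whole grid the range is 0.08 to almost 1.

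If the item excluded the trial's programme and participants followed the wording, both arms would score p0 and the rate would return to 5%.

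**Limit of the calculation.** It compares the arms at one time point. The planned test is an interaction over three waves, and its operating characteristics depend on correlations the article does not give. No figure is offered for the GHSQ, because its response scale is not stated.

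**The case against.** **The questionnaire is not shown.** The article gives item labels, not the stem, instructions or response format. An instruction to disregard the study may exist in the full instrument, and an article would commonly leave it there. This stands as a limit: the point is that the item as worded permits the artefact, not that module use will be counted.

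**The recall window is unknown.** The modules take about 90 minutes in total and are advised one week apart, while the assessments fall at days 91 and 183. With a short window, most module use would lie outside it, above all at 6 months. This also stands, and it could make the artefact small. Against it, the weekly emails invite participants to revisit the site.

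**Participants may not call the modules an information service.** They are an interactive motivational and cognitive behavioural programme. Some will count them and some will not, and the documents do not show how many.

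**A reader might infer that the item can score in the intervention arm only.** The documents do not support that. Both arms use the study website for enrolment and surveys, and the trial website lists contacts for relevant agencies, so a control could endorse the item too. Only the modules and the prompts to use them are specific to one arm.

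**A reader might also take the error rate to be as high as 90%.** That needs 60% of the intervention arm to endorse the item solely because of the trial, with SD 1 (z = 0.60 / 0.1826 = 3.29). Those 60% would all have to be people who would not otherwise have endorsed it. Nothing in the article supports such a figure.

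**Conclusion.** The concern holds in a limited form. The stated item and scoring rule let use of the assigned intervention count as help-seeking, so a time by group difference in the AHSQ, and possibly the GHSQ, can partly reflect allocation.

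The size cannot be determined from the article. Under the stated assumptions the false-positive rate on the summed score lies between near 5% and about 69%, and the upper end needs both heavy endorsement and a small SD. An exclusion in the unseen questionnaire would remove the problem, and a short recall window would reduce it.

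The issue is minor to moderate. It concerns one added item within one of six lettered secondary outcomes. The primary ASSIST score for stimulant use and the sample size are untouched, and the Discussion does not name help-seeking among the measures it calls critical. A reader might conclude that the trial's main result is at risk or that any rise in help-seeking would be spurious. Neither follows.

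**What to change.** First check the questionnaire. If its instructions already exclude the trial's programme, one sentence saying so in the description of the measures settles the matter.

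If not, qualify the added item in the AHSQ, and the matching item in the GHSQ, with *other than this study's website and modules*. The article describes recruitment as still to come, so this costs one line of wording.

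If the wording can no longer be changed, report the AHSQ total with and without this item, and show the item's endorsement by arm at each assessment. This needs one extra scoring rule and no further data or participants. It shows how far an arm difference depends on the item, but it cannot separate module use from outside use within the item, which is why rewording is better.

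Once the item is reworded, it should stay in the total. Dropping it as well is redundant and would discard genuine use of outside internet and telephone services.

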### Estimation of the expected effect sizes and sample size

With three time points (baseline, 3 and 6 months) the study is designed to detect an effect of *f* = .27. This requires 60 people per group: to allow for attrition of 20% by 6 months we will recruit 80 people per group. The development study for the ASSIST reported that in an Australian sample of stimulant users, there was a significant group by time interaction for those who received a brief intervention compared to controls (with 64 and 65 people respectively per group), which had a power of 84% to detect this effect [28]. Other brief in-person motivational interventions have achieved moderate sized effects on drug use measures (*d* = .63-.45) [40], so the effect size postulated for this study is plausible.

### Analysis

The primary analysis will be on an intention-to-treat basis, using a mixed model repeated measures (MMRM) approach. This overcomes many of the limitations of traditional repeated measures analysis of variance, in that it uses all available data without requiring substitution or estimation of missing values to avoid the exclusion of cases with non-complete data and does not assume homogeneity of correlations over waves of measurement [41]. The effect of the intervention will be assessed by an analysis of a time by group interaction. A sensitivity analysis will be conducted using multiple imputation of missing data. Categorical outcome measures will be evaluated using non-linear mixed models.

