Given that psychological treatments can reduce stimulant use [15,18], there is the potential to develop internet-based treatments for ATS users, with many internet-based CBT treatment packages currently accessible via the world wide web [19]. The critical advantage offered by web-based interventions for mental health and substance use problems is that they have the potential to greatly reduce key barriers to obtaining treatment, in particular, stigma (given the anonymous access), cost (with free treatment), reach (potentially worldwide coverage and 24 hour access), especially for those living outside of metropolitan areas [20,21]. This is important in the context of ATS use, not only because of the number of people potentially requiring treatment but because surveys show that stimulant users are reluctant to seek treatment from existing drug treatment services as most are tailored toward clients with opiate or alcohol problems [1,22]. Furthermore, for those with addictive disorders, access to treatment ‘24/7’ may be a particularly important benefit of internet services, allowing the potential to capitalize on times of high motivation to change behavior and access to resources when the risk of relapse is high.

Internet-based interventions have already been demonstrated as effective for the treatment of depression and a range of anxiety disorders [23]. With respect to substance use, web-interventions have been effective in reducing problematic use of alcohol in young adults [24] and in reducing cannabis use via school-based interventions that involve on-line materials [25]. Brief internet interventions have been shown to reduce drug use and ‘high-risk’ behavior in human immunodeficiency virus (HIV) positive drug users [26] and a computerized intervention using combined CBT and motivational interviewing (MI) has been reported to reduce cannabis and alcohol use among those with co-morbid major depression [27]. However, the current authors are not aware of any evaluated internet based interventions for the use of ATS.

The objective of the study was to adapt existing face-to-face psychological approaches (i.e., CBT and MI) for delivery via the internet to reduce the use of ATS and associated problems plus improve motivation to reduce ATS use, with assessment of effectiveness at 3 and 6 months post-intervention.

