**Figure 1 F1:**
[figure not shown]
Participant flow through the study.

Participants who are assigned to the intervention group will then be provided with immediate access to the first module of the intervention. These participants will be advised to allow 1 week between modules, but are allowed to proceed at their own pace. Participants must visit each page of a module in sequence to complete the module and thus obtain access to the next one. The intervention group will receive emails at seven day intervals after the commencement of the trial period, either asking them to start the next module, if they have not already commenced that module, or inviting them to revisit the site. A further e-mail will be sent to those who do not start the current module at 3 days after the module was scheduled for commencement. Participants will be invited via e-mail to complete follow-up assessment at 3 and 6 months (91 and 183 days) post-randomization with a further two reminder emails at 7 day intervals if required, followed by a telephone call(s) for participants who do not respond to the emails. Participants will receive AU$20 for baseline assessment and for each follow-up questionnaire that they complete, paid as either on-line vouchers or posted cheques.

The Australian National University Human Research Ethics committee approved the study, which is also registered with the Australian and New Zealand Clinical Trials Registry (www.anzctr.org.au/) ACTRN12611000947909.

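### The time-by-group interaction, as naturally read, gives each arm its own pre-randomization baseline mean; the test stays valid but loses precision that a common baseline would recover

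*Protocol article*

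**What the plan says.** The Analysis section sets the model: "The primary analysis will be on an intention-to-treat basis, using a mixed model repeated measures (MMRM) approach". It then sets the test of treatment: "The effect of the intervention will be assessed by an analysis of a time by group interaction". Under Measures, "Both the primary and secondary outcome measures will be assessed at baseline, 3 and 6 month". The sample-size section also counts baseline among the modelled occasions: "With three time points (baseline, 3 and 6 months) the study is designed to detect an effect of" f = .27. It continues: "This requires 60 people per group: to allow for attrition of 20% by 6 months we will recruit 80 people per group".

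The Procedure section places the baseline survey before randomization. The article does not say whether the arms are given one baseline mean or two. It names no single contrast or time point as primary. It states no alpha, power or within-person correlation for this trial.

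**The concern.** Because baseline is collected before randomization, any difference between the arms at baseline is chance. A model with a free baseline mean in each arm ignores this. It estimates each follow-up effect as the difference between arms in change from baseline, so the chance imbalance is subtracted in full. With 60 per arm that imbalance has a standard error of sqrt(2/60) = 0.18 SD. A model with a common baseline subtracts only the part that the correlation justifies.

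Precision on the primary outcome is at stake. The loss is large if the ASSIST stimulant score correlates weakly over time and small if it correlates strongly.

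There is also a reporting point. With three occasions and time as a category, the interaction has 2 degrees of freedom. Taken alone, a significant result does not show at which follow-up, or in which direction, the arms differ.

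**Working it through.** **Inputs.** From the article: f = .27, which for two groups is d = 2 x .27 = .54; 60 evaluable per arm; occasions at baseline, 3 and 6 months. Assumed, because the article does not state them: two-sided alpha 0.05, equal variances, one correlation rho between any two occasions (.3, .5 or .7), complete data.

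**The plan's own figure.** The 60 per group cannot be strictly reproduced, because alpha, power and correlation are not given. A two-group 1-df comparison at d = .54 with 60 per arm has 84.1% power (normal approximation; 83.5% by t-test). That is close to the 84% that the section quotes for the cited ASSIST study ("which had a power of 84% to detect this effect"). The 2-df interaction with a free baseline also fits 60: its power is 79% to 83% (F reference) at rho = .40 to .45. So the figure does not show which test was sized. For attrition, 60/0.8 = 75, and recruiting 80 is on the safe side.

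**Variance of one follow-up effect**, in units of 2/n (SD = 1):
- free baseline (difference in change): 2(1-rho) = 1.40, 1.00, 0.60
- common baseline: 1-rho^2 = 0.91, 0.75, 0.51
- reduction: 1-(1+rho)/2 = 35%, 25%, 15%

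**Power of the 2-df test, same effect d at both follow-ups.** With the 2 x 2 covariance of the two follow-up effects, the non-centrality is:
- free baseline: n d^2 / [3(1-rho)]
- common baseline: n d^2 / [(1-rho)(1+2rho)]

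Here n d^2 = 60 x .2916 = 17.496.

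| rho | Non-centrality, free | Power, free | Non-centrality, common | Power, common |
|---|---|---|---|---|
| .3 | 17.496/2.10 = 8.33 | 73.6% | 17.496/1.12 = 15.62 | 95.2% |
| .5 | 17.496/1.50 = 11.66 | 87.4% | 17.496/1.00 = 17.50 | 97.1% |
| .7 | 17.496/0.90 = 19.44 | 98.3% | 17.496/0.72 = 24.30 | 99.6% |

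These are chi-square (known covariance) results. An F reference with 118 denominator df lowers them by at most about one point (72.5, 86.5, 98.0% and 94.7, 96.7, 99.5%). For 80% power the free-baseline test needs 70, 50 and 30 per arm; the common-baseline test needs 38, 34 and 24. At d = .45, the lower end of the range that the article cites in support, power at rho = .5 is 72.3% against 88.7%.

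**Does testing both follow-ups jointly cost power?** With a common baseline and rho = .5:

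| Effect at 3, then 6 months | Joint 2-df | 6 months only | Average of both |
|---|---|---|---|
| .54, .54 | 97.1% | 92.7% | 98.7% |
| .27, .54 | 88.4% | 92.7% | 88.0% |
| .54, .27 | 88.4% | 40.1% | 88.0% |

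No choice is best throughout. The joint test loses to the 6-month contrast only when the effect builds up.

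**What the omnibus result leaves open.** With a free baseline, an effect of .54 at 3 months and zero at 6 has the same non-centrality as .54 at both, and so the same power: 73.6, 87.4 and 98.3%. The test alone cannot tell a lasting effect from one that has gone by 6 months.

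**The case against.** The strongest reply is that the free baseline is inferred. A mixed model with a common baseline also contains time-by-group terms, and a condensed article may leave this detail to a fuller document. The first part stands: the text does not exclude a common baseline. The inference is still the natural one. Baseline is counted as one of three occasions and the interaction is the test of treatment. If baseline were only a covariate, the interaction would compare 3 with 6 months and miss a sustained effect. So the stated test should be clarified even if a common baseline was intended.

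Second, nothing here is invalid. That stands too. In a randomized trial the difference in change scores is unbiased and the type I error rate holds. A fitted mixed model can also supply estimates at each visit. The cost is precision, and it depends on a correlation that the article does not give; at rho = .5 the planned test still has about 87% power for d = .54.

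A reader might infer four stronger claims, which the article does not support:
- *Joint testing in itself wastes power.* The second table shows that it does not.
- *60 per group cannot belong to a 2-df test.* It can, at rho of about .40 to .45.
- *The primary contrast must be 6 months.* The objective covers both follow-ups ("with assessment of effectiveness at 3 and 6 months post-intervention"), and a 6-month contrast has only about 40% power at rho = .5 if the effect fades to .27.
- *The follow-up timing is undefined, because the objective counts from the intervention.* This is loose wording; the Procedure section fixes it: "Participants will be invited via e-mail to complete follow-up assessment at 3 and 6 months (91 and 183 days) post-randomization".

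**Conclusion.** The concern holds as a loss of precision in an otherwise valid analysis. On the natural reading, the primary test gives up information that randomization and the baseline survey already provide. For d = .54 at both follow-ups, 60 per arm and two-sided 0.05, the 2-df test has about 73, 87 and 98% power at rho = .3, .5 and .7. A common baseline raises this to about 95, 97 and 99.5%. The gain is substantial at low correlation and slight at .7. It rests on an assumed equal correlation, complete data and a baseline that really is left free in each arm. Separately, the 2-df result needs time-specific estimates beside it before it can be interpreted.

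**What to change.** 1. Keep the mixed model and state that the arms are constrained to a common baseline mean, so that the time-by-group terms at 3 and 6 months are the treatment effects. Alternatively, enter the baseline ASSIST stimulant score as a covariate and test the group effect over 3 and 6 months, not the interaction between those two visits. The constrained form also keeps participants who have baseline data only.
2. Report the adjusted group difference with 95% CI at each follow-up.
3. State before the data are seen whether the primary contrast is the joint test, the average of both follow-ups or 6 months. This is the sponsor's choice; the second table shows the trade-off.

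The cost is a few sentences in the Analysis section. No extra data or participants are needed, and the article says that recruitment had yet to start. The common baseline has no evident drawback, since randomization guarantees the assumption. Only the choice of contrast involves a trade-off. The objective's time reference can be aligned with the Procedure section in the same edit.
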